## **2.7. Recruitment and Enrollment**

Participants will be primarily recruited from HCMC HIV clinic (Positive Care Center) through provider referral and informational flyers distributed in clinical exam rooms. Referrals will also be accepted from local providers in the Twin Cities. Research ('Solutions') and clinical (EPIC) databases will be queried for to identify eligible patients from our clinic that may be approached directly.

We anticipate that recruitment and enrollment through the HCMC HIV clinic will fill the study after 12-15 months. Recruitment progress will be assessed weekly with research staff. If recruitment is slow, we will encourage referrals from Park Nicollet ID clinic and Allina affiliated HIV clinics. Each of these clinics provides care for another 500-700 HIV-infected patients. In addition, protocol modification with expanded inclusion criteria may be considered after 6 months.

*ADDENDUM – To enhance enrollment, arrangements were made in September 2010 to recruit participants and conducted study visits at the Allina HIV clinic ('Clinic 42') at Abbott Northwestern Hospital in Minneapolis.*

## **3. CLINICAL MANAGEMENT**

### **3.1. Training and Administration of Study Procedures**

A single RN will be trained and perform all study visit procedures at each participating site. Study visits will take approximately 60 minutes. A lab technician will assist with blood specimen processing. Plasma/serum specimens will need to be processed within 30 minutes of collection. Artery waveform data will be transmitted from the HDI tonometer to a PC (as a text file), per instructions in the operator's

manual, after each study visit. CRFs and artery waveform data will be entered into a FileMaker (v9) database.

### 3.2. Participant Safety Monitoring and Withdrawal

Participants will undergo clinical assessment for side effects to study medication at baseline and each follow-up visit (months 1 and 4). Toxicity labs will be assessed per 2.6 above at each study visit, or at any point during the study if symptoms suggestive of drug toxicity/intolerance develop. A clinical pharmacist will participate on protocol team (i.e., [name]) and will review the active clinical medication list upon request for participants prior to enrollment – where potential drug-drug interactions will be identified. Participants taking darunavir (which may increase pravastatin levels to a greater extent than other PIs) will not be excluded from participating from the study, but if a trend is suspected toward more toxicity in these participants then darunavir use may be added to exclusion criteria. Participants may withdraw from the study at any time at their request, as described in the consent.

Participants will be un-blinded to study medication (and will stop any active drug) if toxicity is clinically suspected, or if any of the following criteria are met:

- i. ALT/AST levels double from baseline, increase to  $\geq 10$  x upper limit of normal, or any elevation associated with clinical symptoms.
- ii. CK increase to an absolute level of  $>4$ x upper limit of normal
- iii. Serum creatinine increase  $>0.5$  mg/dL and to an absolute level  $>2.0$  mg/dL; if only one of these criteria are met toxicity labs will be repeated in 2 weeks.
- iv. Blood pressure  $>140/90$ mmHg at baseline and month 1 (lowest value may be used at each visit), when a participant fulfilled the BP thresholds/requirements at screening visit
- v. New clinical indication for ACEi or statin medication that was not present at enrollment

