## **2.2. Outcomes**

### Primary Outcomes

- a. Medication tolerability
  - i. Study withdrawal due to medication side effect (subjective or lab criteria)
  - ii. Discontinuation of a single study medication due to side effect (subjective or lab criteria)
  - iii. Lab measure with  $> 2$  fold increase (with emphasis on: Creatinine, CK, AST, ALT)
- b. Adherence to study medication
  - i. Self report of misses per week
  - ii. Pill count by study RN – reported as % (pills taken/days enrolled in study)
- c. Changes in Framingham risk score (FRS), including serum cholesterol levels and blood pressure

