#### Study Drug:

The choice of drugs for this study was motivated by their efficacy as secondary prevention for CVD events, adjunct anti-inflammatory properties, availability as generic preparations, and potential to counter HIV- and ART-specific CVD risk mechanisms beyond BP and lipid lowering properties. In addition, some statin medications are contraindicated when taking PIs (due to interactions with CYP3A4 pathway), and for this reason pravastatin is the preferred given a lack of metabolism through the CYP3A4 pathway. Darunavir has been noted to increase pravastatin levels to a greater extent than other PIs, and participants taking darunavir will be counseled specifically about this but will not be excluded from participating for this reason.

Both pravastatin and lisinopril are available in generic form. These drugs also have a long track record of being used safely in a clinical setting. Participants for whom BP or cholesterol treatment is indicated will not be enrolled. In addition to clinical monitoring for side effects, toxicity labs will be included at study visit. A clinical doctor of pharmacy (PharmD) is included on the protocol team and will review each participant's medication list upon enrollment. If toxicity to study drugs develop, then participants will be un-blinded and discontinue any active study medication per monitoring criteria below.

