## **2.4. Data Collection**

Details of study will be reviewed with all interested participants. If inclusion criteria are likely based on review of clinic records then a screening visit may be scheduled, where labs and BP will be assessed. Informed consent will be obtained at screening visits. Screening blood draw results will be used to verify blood lipid eligibility criteria (LDLc and TG). The lowest BP reading, taken from up to 3 readings during a screening visit, may be used to assess eligibility criteria. Participants will be given an information pamphlet on ways to reduce heart disease risk at enrollment. If exclusion or withdrawal criteria are met due to BP or lipid level thresholds, then a note with these results will be sent to the participants primary care giver with recommendations that they be evaluated for hypertension or dyslipidemia, respectively.

If eligibility criteria are met, participants will be randomized at the baseline visit to occur within 2 months of screening/consent. After enrollment and baseline visit, participants will present month 1 and month 4 for repeat study procedures. The visit schedule is outlined in the table below. Visits will last approximately 60 minutes.

Toxicity labs and a clinical assessment will be scheduled at any point during the 4 months follow-up if new symptoms develop that may be related to study medications. Toxicity labs and adherence will otherwise be assessed along with study procedures at scheduled 1 and 4 month visits.

**TABLE:** Study procedures and visit timeline

| Measure                      | Screening visit            | Baseline visit       | Symptoms? | Month 1 visit | Month 4 visit |
|------------------------------|----------------------------|----------------------|-----------|---------------|---------------|
| Informed consent             | X                          |                      |           |               |               |
| Randomization                |                            | X                    |           |               |               |
| BP                           | X                          | X                    |           | X             | X             |
| Lipids (TC, HDLc, LDLc, TG)  | X                          | X (if not at screen) |           | X             | X             |
| FRS                          | X                          | X                    |           | X             | X             |

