## 4. ANALYSIS PLAN

The general goal of this pilot study is to gather feasibility and efficacy data, utilizing a 2x2 factorial design (4 cells of  $n=10$ ,  $n=40$  total), to inform planning for a multi-center HIV/CVD polypill trial. We believe treatment with pravastatin (20mg daily) and lisinopril (10mg daily) will be well tolerated and be well adhered to by participants engaged in care and already adherent to ART. We hypothesize that Framingham risk score will improve with either drug intervention. Future sample size estimates will be generated from effect size related to changes in arterial elasticity and biomarkers.

**Primary Analyses:** Mean changes in FRS after 4 months will be studied with pravastatin use (versus placebo) and lisinopril use (versus placebo). The effect of both drugs combined, compared with double-placebo, will also be examined. Adherence and the frequency of intolerability, based on subjective or lab criteria, will also be compared between groups using the definitions listed in ‘outcomes’ (2.2). Elevations in lab values will also be categorized by severity (using established grades 1-4).

**Secondary Analyses:** Mean changes in hsCRP, IL-6, D-dimer, SAE, ApoB, ApoA1, and LDL and HDL particle concentrations will be studied after 4 months of pravastatin and lisinopril, given alone or in combination, using similar methods as above in primary analyses. Tests for correlation between change in these markers and BP, total cholesterol and FRS will also be considered. Regression models may be

considered to adjust for additional clinical characteristics (including, but not limited to traditional CVD risk factors), but power will be quite limited for these analyses.

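### The toxicity rule un-blinds first and then mandates stopping active drug only, so side-effect discontinuations (primary outcomes a.i/a.ii) are not ascertained alike on active and placebo

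*Combined protocol and SAP*

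**What the plan says.** Section 3.2 sets the rule: "Participants will be un-blinded to study medication (and will stop any active drug) if toxicity is clinically suspected". The same action applies when one of five listed triggers is reached: liver enzymes, CK, creatinine, blood pressure, and a new indication for either drug class. Section 2.3 (Study Drug) gives the same rule: "participants will be un-blinded and discontinue any active study medication per monitoring criteria below". Both places limit the mandatory stop to active drug. Neither says whether a triggered placebo pill is stopped, continued or counted.

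Section 2.2 lists tolerability first among the primary outcomes. Item a.i is "Study withdrawal due to medication side effect (subjective or lab criteria"), item a.ii is "Discontinuation of a single study medication due to side effect (subjective or lab criteria"), and item a.iii is a laboratory rise of more than 2-fold.

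Section 4 says: "Adherence and the frequency of intolerability, based on subjective or lab criteria, will also be compared between groups", using the section 2.2 definitions. It also grades laboratory elevations by severity. It names no test for tolerability and gives no rule for counting stops. Section 2.4 keeps investigators, staff and participants blinded to allocation. No section says that a toxicity event is classified before the code is opened.

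**The concern.** A tolerability comparison is fair when the same clinical event is recorded the same way whichever capsule the participant holds. Here the code is opened at the trigger, and the action that defines the outcome then depends on what the code shows. Two participants with the same complaint can end differently: the one on active drug must stop, and for the one on placebo nothing is mandated. Part of the outcome is then produced by the allocation rather than by the drug.

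The factorial layout adds a second dependence. Item a.ii concerns one pill. A triggered participant on both drugs must stop two and so may leave a.ii for a.i, or fall under neither. Which item records the event therefore also depends on the cell.

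The pilot is meant to inform a multi-center polypill trial. Stop rates that look worse on active drug for procedural reasons would carry over into the assessment of feasibility. In a trial of 40 the reported rates matter more than any test, and one or two extra stops change them visibly.

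**Working it through.** **The plan's own figure.** The documents give no figure for tolerability. The only sample-size statement (section 2.5) is for the Framingham score: 20 per group to detect 0.9 SD with 80% power, two-sided 0.05. It reproduces: n = 2 × (1.960 + 0.842)² / 0.9² = 19.4, rounded up to 20. It has no bearing on this point beyond confirming the 20 v 20 margins.

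**Inputs.** From section 4: four cells of 10. From sections 2.3 and 3.2: on a trigger, every active pill stops. Assumed, because the documents are silent: a trigger rate p that is equal in all four cells (no drug effect), triggers treated as side effects, and no placebo pill stopped.

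**Step 1. Expected mandated stops by cell.**

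| Cell (n = 10) | Triggered participants | Pravastatin stops | Lisinopril stops | Participants stopping exactly one drug |
|---|---|---|---|---|
| Double placebo | 10p | 0 | 0 | 0 |
| Pravastatin only | 10p | 10p | 0 | 10p |
| Lisinopril only | 10p | 0 | 10p | 10p |
| Both drugs | 10p | 10p | 10p | 0 (each stops two) |

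**Step 2. Expected counts for each drug comparison.**

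| Counting rule | Formula | p = 5% | p = 10% | p = 20% |
|---|---|---|---|---|
| All stops (a.i and a.ii together), by drug, per 20 | 10p + 10p v 0 | 1 v 0 | 2 v 0 | 4 v 0 |
| All stops, by participant, per 20 | 20p v 10p | 1 v 0.5 | 2 v 1 | 4 v 2 |
| Single-drug stops (a.ii alone), by drug, per 20 | 10p v 0 | 0.5 v 0 | 1 v 0 | 2 v 0 |
| Single-drug stops, by participant, per 20 | 10p v 10p | 0.5 v 0.5 | 1 v 1 | 2 v 2 |
| Single-drug stops, one-drug cell v double placebo, per 10 | 10p v 0 | 0.5 v 0 | 1 v 0 | 2 v 0 |

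The fourth row balances because the lisinopril-only cell supplies the stops on the no-pravastatin side, and the reverse for the lisinopril comparison. The imbalance has not gone. It reappears against double placebo (last row), and the double stops still have to be counted somewhere.

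**Step 3. Dependence on how placebo is handled.** Let s be the share of triggered placebo pills also stopped (assumed). All stops by drug become 20p v 20ps. At p = 10% this is 2 v 0 for s = 0, 2 v 1 for s = 0.5 and 2 v 2 for s = 1. If every trigger is counted alike, the bias is zero.

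**Step 4. What the allocation-independent measures cover.**
- Trigger i (doubling of ALT/AST) nearly matches the more-than-2-fold rise in a.iii. A smaller elevation with symptoms does not.
- Trigger ii (CK above 4 times the upper limit) implies a more-than-2-fold rise whenever baseline CK is at or below 2 times that limit.
- Trigger iii can be met without a.iii. For example, creatinine going from 1.6 to 2.2 mg/dL is a rise of 0.6 to a level above 2.0, but only 2.2/1.6 = 1.4-fold.
- Toxicity suspected from symptoms alone has no counterpart in a.iii or in the lab grades.
- Triggers iv and v (blood pressure, new indication) are not side effects and so do not meet a.i or a.ii as worded.

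**The case against.** The strongest reply is that the outcome can be read as criterion-based. Section 4 speaks of intolerability judged on subjective or laboratory criteria, and such criteria do not depend on allocation. The trigger list sits under a heading that includes withdrawal, and section 2.4 begins a sentence "If exclusion or withdrawal criteria are met due to BP or lipid level thresholds", so the triggers may be withdrawal criteria that apply to everyone. Nothing forbids stopping a placebo pill, and voluntary stops while still blinded count in every arm. This stands as a possible reading, and it leaves the effect on a.i uncertain. It does not close the gap: no section counts a triggered placebo participant as a discontinuation, and two sections confine the mandated stop to active drug.

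A second reply is that most laboratory toxicity is caught alike in all arms by a.iii and the lab grades. That is largely right. It narrows the problem to symptom-suspected toxicity and a few laboratory cases.

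Two stronger readings are tempting, and the documents do not support them.
- A reader might infer that a.ii itself is inflated two to one, or 2 v 0, on active drug. Those counts include participants who stop both pills, and a.ii is worded for a single medication. Taken strictly, a.ii gives half the by-drug count, and no marginal difference by participant.
- A reader might apply Fisher's exact test and infer a large risk of a false significant finding: 37% for all stops by drug at a 20% trigger rate with no placebo stopped. The same calculation for single-drug stops gives 3.3%. Neither is a property of this trial. No test is planned for tolerability, the 0.05 level in section 2.5 belongs to the Framingham score, and the trigger rate is assumed.

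**Conclusion.** The concern holds in limited form. As written, protocol-triggered discontinuation is mandated on active drug and not on placebo, after the code has been opened, and it feeds primary outcomes that are compared between groups. A spurious excess of stops on active treatment can follow with no drug effect.

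Its size cannot be taken from the documents. The illustration at a 10% trigger rate ranges from no marginal difference (a.ii by participant) to 2 v 0 per 20 (all stops by drug). It rests on the literal reading of the rule, equal trigger rates in all cells and no placebo pill stopped. That the answer moves this much with an unwritten counting rule is itself part of the finding. The severity lies between minor and should-fix.

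**What to change.** Before the code is opened, record on the case report form the trigger met, the drug or drugs suspected, and the stop decision for each pill. Define a.i and a.ii from that blinded record and count it identically in every arm, whatever the code then shows. State in section 2.2 or section 4 whether stops are counted by drug or by participant, and whether a participant who stops both pills belongs to a.i or a.ii.

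Safety un-blinding stays as it is. No extra instruction is needed for the blood pressure and new-indication triggers, since a.i and a.ii already require a side effect. The cost is one case report form line and wording in sections 2.2, 3.2 and 4, with no added visits or participants. It has to be set in advance, because the blinded judgement cannot be rebuilt without bias once allocation is known.

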## **2.3. Design Justification**

### General Design:

A randomized trial design will control for both known and unknown confounders, and the 2X2 factorial design will allow separate evaluation of the treatment interventions. Visit frequency was chosen to evaluate short-term tolerability and risk factor changes in an efficient manner with this initial pilot phase. Other CVD risk factors, such as smoking, will not specifically be targeted in the context of study visits so as not to confound the effect of pravastatin and/or lisinopril.

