## 2.5. Sample Size Considerations

With a total sample size of 40 patients (20 per group for comparison of each drug intervention), a  $0.9 \times SD$  (standard deviation) difference in 10-year Framingham risk score from each drug can be detected with 80% power at the 0.05 (2-sided) level of significance. The variability in Framingham risk score was estimated from the Multiple Risk Factor Intervention Trial (MRFIT), where the estimated SD based on 11,702 participants was 0.20, corresponding to a relative change of approximately 20%. Thus, a  $0.9 \times SD$  change in this pilot study would correspond to an 18% relative change in Framingham risk score over the follow up period. Thus a change in Framingham risk of 8% to 6.5% would be  $>18\%$  relative improvement. In this proposal, if a 40-year old male smoker with SPB of 130mmHg, TC of 190mg/dL,

HDLc 35mg/dL demonstrated a reduction in SBP of -5mmHg and TC of -20mg/dL, and no increase in HDLc, his 10-year Framingham risk score would have a 25% relative improvement (8% to 5%). This is a very reasonable estimate as a mean change in TC of -40mg/dL after 12 weeks of pravastatin treatment was reported among 86 HIV-infected participants, and patients in our HCMC clinic commonly have lipid profiles less favorable than this.

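### For the non-toxicity triggers in section 3.2 (raised BP, new ACEi or statin indication), un-blind and stop only the study drug concerned, not both

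*Combined protocol and SAP*

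**What the plan says.** The rule is in section 3.2: "Participants will be un-blinded to study medication (and will stop any active drug) if toxicity is clinically suspected", or if one of items i to v is met. Items i to iii are limits for ALT/AST, CK and creatinine. Item iv is BP above 140/90 mmHg at both baseline and month 1, "when a participant fulfilled the BP thresholds/requirements at screening visit". Item v reads "New clinical indication for ACEi or statin medication that was not present at enrollment". The same action follows from all five, and nothing ties it to one of the two drugs.

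Four other places bear on this:

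- Section 2.3, Study Drug, gives the reason for the rule as toxicity only: "If toxicity to study drugs develop, then participants will be un-blinded and discontinue any active study medication per monitoring criteria below".
- Section 2.3, General Design, gives the reason for the factorial layout: "the 2X2 factorial design will allow separate evaluation of the treatment interventions".
- Section 2.2, outcome a.ii, foresees stopping one study medication alone, but only for a side effect.
- Section 2.4 uses withdrawal language: "If exclusion or withdrawal criteria are met due to BP or lipid level thresholds", a note goes to the primary care giver. It does not say what then happens to study drug or follow-up.

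The primary efficacy analysis (section 4) takes each drug's contrast at the end of follow-up: "Mean changes in FRS after 4 months will be studied with pravastatin use (versus placebo) and lisinopril use (versus placebo").

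**The concern.** Stopping everything is defensible when toxicity is suspected, because the responsible drug may not be known. That reason does not extend to items iv and v. A participant who newly needs a statin has shown nothing against lisinopril, and one whose BP is high at baseline and month 1 has shown nothing against pravastatin. As written, both drugs end if active, and both allocations are revealed.

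This links the two factors. Item iv can be met only once month 1 is reached, three months before the endpoint, and an item v event may also come early. The other drug's month-4 contrast then includes participants who are no longer taking it, for a reason unrelated to its tolerability or effect. Its blind is lost in those participants as well, including those on its placebo, who have nothing active to stop. The same applies to the elasticity and biomarker changes from which section 4 will plan the next trial.

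**Working it through.** **1. The plan's own figure.** Inputs from section 2.5: "With a total sample size of 40 patients (20 per group for comparison of each drug intervention"), a 0.9 SD difference, two-sided 0.05, 80% power.

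- Normal approximation: 0.9 × √(20/2) = 2.846; 2.846 − 1.960 = 0.886; power 81.2%.
- Two-sample t-test (38 df): power 79.2%.

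Both agree with the stated 80%. The t-test is used below.

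**2. Which drug is lost under each trigger, as written and with a drug-specific stop.**

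| Trigger | Drug concerned | Other active drug stopped as written? | With a drug-specific stop |
|---|---|---|---|
| Item iv, BP | lisinopril | yes, pravastatin | continues blinded |
| Item v, ACEi indication only | lisinopril | yes, pravastatin | continues blinded |
| Item v, statin indication only | pravastatin | yes, lisinopril | continues blinded |
| Item v, both classes indicated | both | not applicable | both stop |

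**3. Size per stop.** Suppose k of the 20 active users of the other drug stop at month 1, have no effect left at month 4, and are analysed as randomised. The expected contrast is then 0.9 × (20 − k)/20 SD.

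| k | Contrast (SD) | Loss | t-test power |
|---|---|---|---|
| 0 | 0.900 | 0% | 79.2% |
| 1 | 0.855 | 5% | 75.0% |
| 2 | 0.810 | 10% | 70.4% |

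Any residual effect at month 4 makes the loss smaller, so 5% per stop is an upper figure.

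**4. How many stops.** The documents give no rate. The ranges below come from simulation with assumed inputs and show only the order of magnitude.

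- *Item iv.* Assumed: mean SBP 120 to 125 (SD 12 to 14), mean DBP 76 to 80 (SD 8 to 9), correlation 0.6, systolic visit-to-visit SD 6 to 9 mmHg (diastolic 0.65 times that), reading SD 4/3 mmHg, lowest of three readings at each visit, lisinopril effect −4/−2.5 to −8/−5 mmHg. Expected pravastatin users stopped: about 0.15 to 0.75 of 20.
- *Item v, lipids.* Assumed: LDLc mean 110 to 120 mg/dL (SD 28 to 30), within-person CV 8 to 10%, pravastatin effect −10 to −25%, and every single month-1 reading at or above the section 2.1 limit acted on. Expected lisinopril users stopped: about 0.2 to 0.65 of 20 if all participants have FRS below 10%, and 0.5 to 1.2 if half have FRS 10 to 20%.

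Most of these are below one expected stop. The lipid figures are upper ones, because item v asks for a clinical indication and not one reading over a limit. The true number may be 0.

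**The case against.** **The wording may be looser than the intent.** Outcome a.ii expects that one study medication can be stopped alone. With both drugs active, a rule that always stops everything would leave that outcome empty. The phrase in section 3.2 may therefore mean the drug in question, if active. This is a fair reading, but a.ii is confined to side effects, so nothing in the text applies it to items iv and v. It does show that a single-drug stop is workable in this trial.

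**The other drug is not always unrelated.** New CVD or diabetes would breach a general entry condition (section 2.1), not one factor's. The LDLc limits depend on FRS, and FRS includes systolic BP and use of BP treatment (section 2.6), so a BP trigger can change the lipid limit that applies. Stopping both is then reasonable. This stands, and it sets the exception in the fix. It does not cover an indication confined to one class.

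**The size is small and assumed.** This stands too. A reader might infer from the table that power really falls to 70.4%. That needs two stops of users of the same drug, and the documents support no such number. A reader might also infer that the next trial's sample size would be materially distorted. One stop shifts the estimate by 0.9 − 0.855 = 0.045 SD, against a standard error of √(2/20) = 0.316 SD, which is well within the pilot's own imprecision.

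**Follow-up may already be intended.** Section 2.4 schedules month 4 for participants in general, section 2.2 separates study withdrawal from stopping a drug, and section 3.2 orders drug to be stopped, not the participant to leave. A reader might infer from the withdrawal wording in section 2.4 that these participants are dropped from the month-4 analysis. The documents do not say so. They also do not say the opposite, and the consent form, to which section 3.2 refers for withdrawal at a participant's request, was not available. The lack of an as-randomised statement is a general omission in section 4, not a fault particular to items iv and v.

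**Conclusion.** The concern holds as a minor point about a stated rule. As written, items iv and v end and un-blind a study drug that the trigger does not concern, and the only reason given for the rule, toxicity, does not reach them. This runs against the stated purpose of the factorial design.

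The cost is up to 5% of the other drug's contrast per stop (79.2% to 75.0% power for the first), assuming 20 per group, a true 0.9 SD effect, a stop at month 1 and no residual effect at month 4. The number of stops is unknown and may be 0. The documents do not support the stronger conclusion that the factorial comparison is invalid or that the trial is materially underpowered because of this rule. The case for changing it is that the loss can be avoided for single-class triggers at almost no cost.

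**What to change.** In section 3.2, give items iv and v their own action:

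- Item iv, or an indication for an ACEi only: un-blind and stop lisinopril/placebo only.
- An indication for a statin only: un-blind and stop pravastatin/placebo only.
- In both cases, continue the other study drug blinded.
- If the new condition indicates both classes, or would make the participant ineligible in general (for example new CVD or diabetes), stop both.

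Leave items i to iii, and the rule for clinically suspected toxicity, unchanged. State in sections 3.2 and 4 that participants stopped under items iv or v stay in follow-up to month 4 and are analysed as randomised. In section 2.4, speak of criteria for stopping a study drug in place of withdrawal criteria.

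The cost is a few sentences and a code break that reveals one factor only, which is slightly more complex to run; a pharmacist already has access to the code (section 2.4). No participants, visits or tests are added, and toxicity protection is unchanged. For triggers confined to one class, the loss of the other drug falls to zero. It remains where both classes are indicated.
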